#### Overview of Naltrexone Trial

The purpose of the study is to evaluate whether AGATE effectively measures and enhances medication adherence in the context of a naltrexone trial involving heavy drinkers. Participants will be heavy drinkers recruited from the greater Albuquerque area who are interested in either reducing or stopping their drinking and deemed to be candidates for naltrexone pharmacotherapy by the study physician, [name]. Those enrolled in the study will be prescribed naltrexone (at FDA-approved dose of 50mg once daily) for eight weeks. All participants will receive smartphones during the study. Participants will be randomly assigned to receive either AGATE (adherence support) or SASED, a web-based alcohol and side-effects diary via smartphone. The primary outcome will be percent of scheduled doses that were taken during the eight week trial, as measured by the Medication Event Monitoring System (MEMS, Aardex Group, Union City, CA), pill counts, and the timeline follow-back (TLFB) method. The secondary outcomes will be selected indicators of alcohol use over the 8-week trial.

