Participants will next provide informed consent (see attached consent form). They will then provide a urine sample in a private bathroom at for purposes of a toxicology screen. Additionally, female participants will complete a urine-based pregnancy screen (in the event of a positive result, the participant will not be allowed to continue with the study). Participants will next report to the UNM Psychiatry Department Pharmacy (in the building adjoined to MRN) for blood work. A licensed phlebotomist will acquire a small blood sample (approximately 12-15ml) to test for complete blood count (CBC) and a liver enzyme panel, including examining levels of gamma-glutamyl transferase (GGT), to ensure that participants are appropriate candidates for naltrexone

treatment. Blood samples will be labeled by URSI number and sent to TriCore laboratories. A TriCore representative will pick up the samples on the collection day.

When participants' blood/urine samples have been analyzed (estimated 2-3 days after the screening visit), results will be placed in the participant's research study folder at MRN for review by [name], along with results of the pregnancy screen. If the patient is deemed a candidate for naltrexone based on blood/urine screens (see exclusion criteria), they will be scheduled for their baseline (Week 0) appointment. At that time, participants will be asked to remain abstinent from alcohol for 72 hours prior to their appointment to permit an assessment of potential withdrawal. If the patient is not medically eligible for naltrexone based on blood/urine screens, the [name] will call the participant to discuss the results, inform the participant of ineligibility, and provide a referral if indicated.

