Finally, the participant will pick up his/her 4-week prescription for naltrexone at the UNM Psychiatry Department pharmacy. The pill container will be fitted with a MEMS monitoring system by the pharmacist, which will track the date/time of each time the container is opened. This data, which is stored in a microchip in the MEMS cap. The pillcap will not be linked to any personal identifier or URSI. The data will be downloaded when the participant returns for subsequent visits and labeled by URSI at that point. Data (timestamps) on pillcap openings will be linked to URSI in a password-protected spreadsheet kept on a password-protected computer at MRN. At the end of the baseline appointment participants will be encouraged to contact the study coordinator with any questions, concerns, or problems related to study participation. They will also be encouraged to contact [name] directly with any questions about the study medication or side effects.

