Following the baseline visit, the course of the medication trial will be 8 weeks. During this time participants will come back to MRN/UNM CPR for follow-up medical visits (at weeks 4 and 8). This timeframe is consistent with recommended clinical guidelines for monitoring patients on naltrexone (Anton, 2008). At the Week 4 visit, participants will first be interviewed by the research assistant, who will assess potential side effects using a standard side effects checklist. Results of the interview (i.e., any side effects reported) will be placed in the research folder for [name] to review. Participants will also bring medication bottles for pill counts and uploading of MEMS pillcap data. They will report whether they have had any problems with their study phone or AGATE system.. Participants will report whether they have had any problems with their study phone. Any problems will be documented and addressed. Participants will also complete a brief subset of the study questionnaires again (e.g., assessing drinking and medication adherence in the last 4 weeks, see Table 1). Similar to the baseline visit, participants will be seated alone in a private assessment room at MRN and will complete measures using the web-based interface. Next, a follow-up blood sample will be obtained in the Psychiatry pharmacy using the same procedures and tests as described in the screening visit. Then the participant will meet with [name] for a follow-up medical assessment. [name] will review the contents of the participant's research study folder (e.g., side effect checklist) and interview the participant. If any medical contraindications to continuing naltrexone are evidenced, naltrexone treatment will be discontinued immediately. In these cases, [name] will discuss with the participant an appropriate referral plan. To avoid threats to internal validity, [name] will be blind to study condition (AGATE/SASED). For this reason, she will not discuss aspects of AGATE or barriers to adherence with participants; the interview will be focused on side effects and medical/safety issues. If no contraindications to continuing naltrexone are evidenced, participants will be provided with the next 4-week naltrexone prescription, which will be sent to the pharmacy. Again, pill vials will

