be re-fitted with a MEMS monitoring system pillcap. Participants will not be allowed to take home their prescription on this day, pending results of the blood screen. When the results of the Week 4 blood screen are available, they will be placed in the study chart for review by [name]. If no problems with the bloodwork are evidenced, the research assistant will contact the participant and ask that they pick up their prescription from the pharmacy. If any concerns are noted that suggest medication should be discontinued, [name] will call the participant to inform them.

At week 8 the study physician will complete a visit identical to week 4 (i.e., it will include the same questionnaires, pill counts, blood draw, and medical visit). However, participants will be discharged at the end of the week 8 visit. At the medical assessment, [name] will provide a discharge recommendation. Participants who show evidence of a good clinical outcome to naltrexone will be referred to their PCP. At the end of the 8 week visit the study coordinator will also conduct an exit interview to elicit qualitative information on the usability and acceptability of AGATE/SASED.

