AGATE was designed so that the patient and provider agree upon (or the researcher sets) an adherence goal (e.g. a minimum of 90% of scheduled doses to be taken) over a certain period of time (e.g., 14 days). In the first stage, patients (or research participants) receive a reminder/assessment message for every scheduled dose. If at the end of this period the patient has achieved the goal, the patient progresses to Stage 2, in which the reminder/assessment frequency steps down (e.g., once every few days) for another period of time (e.g., 21 days). If at the end of this period the goal is maintained, the patient progresses to Stage 3, in which the reminder/assessment frequency steps down further (e.g., once per week). However, if the goal is *not* maintained in Stage 2 or 3, messaging frequency steps back up, and patients return to the preceding stage. In this context patients will be provided regular feedback on their performance and reminded of their goal. Participants will also complete daily assessments of drinking behavior (e.g., number of standard drinks per day, urge to drink) throughout the study using the AGATE system. Talaria will collect online metrics of number of messages ignored versus answered and latency to respond to messages to gauge the use/uptake of AGATE and SASED. For the current study, SMS reminders to take medication will be tailored based on the participant's level of adherence to that point. At the outset, participants will be reminded daily to take their medication. Upon achieving adherence for a period several days, reminders will be reduced to once every third day. Please see Appendix V for an example of the AGATE messaging parameters (frequency of reminders, etc).

Participants in the control (SASED) condition will not receive any medication reminders. However, all

participants (AGATE and SASSED) will complete daily drinking measures (e.g., number of standard drinks per day, urge to drink) via the smartphone interface; these assessments will be sent each morning and will be identical across treatment condition.

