v) Describe Informed Consent procedures, including parental/guardian permission and minor assent for studies involving minors. Address any additional measures to be taken with any vulnerable populations. If you are requesting a waiver of informed consent, indicate request and justifications.

- Pre-enrollment: Participant completes phone screen.
- Screening visit: Research assistant provides participant with an overview of the study and provides the

consent form; participant provides informed consent by signing the consent form if they choose. Participant provides blood/urine samples.

- Week 0: Participant completes baseline medical evaluation. If all inclusion criteria and no exclusion criteria are fulfilled to that point, participant receives prescription and is issued a study smartphone.
- Weeks 4 and 8: Return visits for medical interview; blood draw; questionnaires.
- Weeks 0-8: Participant completes daily measures of drinking/adherence; those assigned to AGATE receive medication reminders.

For all recruitment and screening contacts emphasis will be placed on the voluntary nature of the study. Participants will be provided with as much time as they wish to read the consent form and decide upon participation. The ability for participants to withdraw without penalty anytime over the course of the study will be emphasized.

The payments are consistent with ongoing studies in [name] lab, and are not large enough so as to be coercive. Although participants will be allowed to keep their cell phone following the study, we will minimize undue influence by informing them of this after enrollment, not during recruitment.

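### The week-4 blood hold can leave a fully adherent participant without tablets for about 2-3 days, in a trial that scores the percentage of doses taken

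*Protocol*

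**What the plan says.** All of the supply steps are in Protocol section V.i, Overview of Naltrexone Trial and the Procedures text under it. Naltrexone is taken once daily for eight weeks. At the end of the baseline visit "the participant will pick up his/her 4-week prescription for naltrexone". Follow-up visits are at weeks 4 and 8. At week 4 a blood sample is drawn "using the same procedures and tests as described in the screening visit"; for the screening samples, analysis was "estimated 2-3 days after the screening visit". The second four-week supply is ordered at that visit, but "Participants will not be allowed to take home their prescription on this day, pending results of the blood screen". It is released only after the physician has seen the result, the research assistant has contacted the participant, and the participant has gone to the pharmacy.

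On the outcome, the same section says: "The primary outcome will be percent of scheduled doses that were taken during the eight week trial". On the intervention, the timeline in section VI.v reads: "Weeks 0-8: Participant completes daily measures of drinking/adherence; those assigned to AGATE receive medication reminders". The Overview of AGATE describes an adherence goal, illustrated as "a minimum of 90% of scheduled doses to be taken", and says that if the goal is missed in a later stage "messaging frequency steps back up, and patients return to the preceding stage". The study's own messaging settings are referred to Appendix V, which is not shown.

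**The concern.** A four-week supply, a resupply visit at four weeks and a hold at that visit do not fit together. A participant who has followed every instruction reaches the visit with an empty bottle and must then wait for a laboratory result. Nothing in the protocol bridges the wait, and the analysis plan could not do so, because the problem is one of supply.

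Two things are at stake. First, the primary outcome would record missed doses that the protocol caused. These would fall mainly on the most adherent participants, because those who had skipped doses may still have tablets left. Second, AGATE participants could be reminded to take a tablet they do not have and, depending on the settings, could be moved back to more frequent reminders for a reason unrelated to their behaviour.

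**Working it through.** The protocol gives no figure for this point, so there is none to reproduce. The check is dose arithmetic.

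**Inputs**
- Scheduled doses: once daily for eight weeks, so 8 × 7 = 56 (derived; the protocol does not state 56).
- First supply T: four weeks, so 28 tablets if dispensed exactly (assumption; no tablet count is given).
- Visit day v: about 28 (assumption; no visit window is given).
- Hold h: 2-3 days, the screening estimate, carried to week 4 because the procedures and tests are the same.
- Adherent class: 80% or more of scheduled doses (section III, Hypothesis 1).
- AGATE example settings: 90% goal, a 14-day first stage and a 21-day second stage (Overview of AGATE).

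**Days without tablets for a participant who took every dose**

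Days short = max(0, v + h − T).
- v = 28, T = 28: 2 days (h = 2) or 3 days (h = 3).
- v = 28, T = 30: 0 or 1 day. With T = 31: 0 in both cases.
- v = 26 with h = 2, or v = 25 with h = 3, T = 28: 0 days.
- A late visit, or time lost in contact and pick-up, adds to the gap.

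**Ceiling on the primary outcome, literal 56-dose count**
- 2 days short: 54/56 = 96.4%.
- 3 days short: 53/56 = 94.6%.
- 5 days short, if contact and pick-up are slow: 51/56 = 91.1%.

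**80% classification**

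0.80 × 56 = 44.8, so 45 doses are needed. A fully adherent participant has 54 or 53 and is still classed as adherent.

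**AGATE reminders**

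In this study reminders start daily and fall to every third day after several adherent days. A fully adherent participant would therefore get one reminder in a 3-day hold, and none or one in a 2-day hold. A participant still on daily reminders would get 2-3.

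**AGATE step-up rule, example settings**

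A fully adherent participant passes the first stage on day 14. The second stage then runs from day 15 to day 35 and contains the held days, 29-30 or 29-31. If AGATE counts each held day as missed:
- 2-day hold: 19/21 = 90.5%, goal met.
- 3-day hold: 18/21 = 85.7%, goal missed.

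**Effect on the difference in means**

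If leftover tablets are collected at the visit, nobody can dose during the hold. Everyone's expected percentage is multiplied by 54/56 or 53/56, so the arm difference shrinks by 2/56 = 3.6% or 3/56 = 5.4%. If leftovers are kept, less adherent participants can dose through the hold and fully adherent ones cannot. The loss then depends on the distribution of adherence in each arm, for which the protocol gives no AGATE figure.

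**The case against.** The strongest reply is that the gap is inferred. The protocol states no tablet count, visit window or week-4 turnaround, and a couple of extra tablets or a visit on day 25 or 26 would shrink or remove it. This stands as a limit on size. It does not remove the point, because an exact four-week supply and a visit at four weeks are the plain reading of the plan, and on that reading the gap occurs.

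A second reply is that the treatment of withheld days in the denominator belongs in the analysis plan, and the reminder settings in Appendix V. That also stands: silence on those two matters would not be a finding by itself. The supply timing is different, because the protocol fixes it.

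Third, the hold is a deliberate liver-safety step. It should be kept, and the fix below keeps it.

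A reader might go further in three ways that the document does not support:
- **A biased comparison.** The hold applies equally to both arms and creates no false effect.
- **A large loss of effect or power.** Any such figure needs an assumed mean and spread for AGATE, and a large one needs most AGATE participants to be almost perfectly adherent, together with an exact 28 tablets, a day-28 visit and leftovers kept.
- **Failure of the example 14-day goal.** A fully adherent participant has left that stage by day 14, well before the hold.

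**Conclusion.** The point holds, as a minor one. As written, and assuming 28 tablets, a visit at about day 28 and the screening turnaround, the plan makes a fully adherent participant miss about 2-3 doses. This caps the primary outcome at 96.4% or 94.6% on a literal count. AGATE participants can be reminded during those days. On the example settings, a 3-day hold but not a 2-day hold would also move a fully adherent participant back a stage; the study's own settings are not shown.

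The hold does not change the 80% classification of a fully adherent participant. Any dilution of the difference in mean adherence is small to moderate and depends on tablet count, visit day and whether leftover tablets are kept. Confidence is medium, because those three facts are not stated.

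**What to change.** Take the follow-up blood sample, or hold the whole week-4 visit, 4-5 days before the first supply ends, at about day 23-24. With a 3-day turnaround the result is back by day 26-27 (23 + 3 or 24 + 3), which leaves one or two days for review, the call and pick-up before a 28-tablet supply runs out. This remains consistent with the liver-test timing of roughly one month in section VI.vi (Medication), and the result is still reviewed before any second supply is released.

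As a supporting clarification, state that any remaining days on which the protocol withholds naltrexone are not scheduled doses, both in the primary outcome and in AGATE's adherence calculation. A fully adherent participant would then score 54/54 or 53/53 = 100%, and the hold could not cause a missed goal.

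The cost is a few sentences of protocol text and either a slightly earlier visit or one short separate blood draw.

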## **SMARTPHONE REMINDERS AND ASSESSMENTS**

### **Overview of AGATE**

Talaria has developed AGATE, an adaptive goal-directed adherence tracking and enhancement system for cell phones. To summarize, AGATE uses a combination of Short Message Service (SMS) text messages and internet access on a cellular handset to remind and assess medication adherence. On many handsets (e.g., Windows Mobile, iPhone, Blackberry, and others), SMS messages permit the inclusion of live hyperlinks that can launch web-based assessments, conducted via the internet. An administrator registers the participant in the database, using the email-to-SMS gateway address for the participant's phone. All major carriers in the US and abroad make it possible for their cellular subscribers to receive SMS messages via email by providing email addresses for this purpose. Thus, it is only necessary to know the participant's cell phone number and carrier. AGATE offers a simple and elegant yet powerful solution to the problem of medication adherence.

For a visual summary of the AGATE interface, as well as examples of questions assessing alcohol use and medication adherence, please see Appendix IV for an excerpt from Talaria's technical report from the development of AGATE in the aforementioned Phase I SBIR study. Note that the Phase I study used HIV medication as the hypothetical target medication.

AGATE was designed so that the patient and provider agree upon (or the researcher sets) an adherence goal (e.g. a minimum of 90% of scheduled doses to be taken) over a certain period of time (e.g., 14 days). In the first stage, patients (or research participants) receive a reminder/assessment message for every scheduled dose. If at the end of this period the patient has achieved the goal, the patient progresses to Stage 2, in which the reminder/assessment frequency steps down (e.g., once every few days) for another period of time (e.g., 21 days). If at the end of this period the goal is maintained, the patient progresses to Stage 3, in which the reminder/assessment frequency steps down further (e.g., once per week). However, if the goal is *not* maintained in Stage 2 or 3, messaging frequency steps back up, and patients return to the preceding stage. In this context patients will be provided regular feedback on their performance and reminded of their goal. Participants will also complete daily assessments of drinking behavior (e.g., number of standard drinks per day, urge to drink) throughout the study using the AGATE system. Talaria will collect online metrics of number of messages ignored versus answered and latency to respond to messages to gauge the use/uptake of AGATE and SASED. For the current study, SMS reminders to take medication will be tailored based on the participant's level of adherence to that point. At the outset, participants will be reminded daily to take their medication. Upon achieving adherence for a period several days, reminders will be reduced to once every third day. Please see Appendix V for an example of the AGATE messaging parameters (frequency of reminders, etc).

Participants in the control (SASED) condition will not receive any medication reminders. However, all

participants (AGATE and SASSED) will complete daily drinking measures (e.g., number of standard drinks per day, urge to drink) via the smartphone interface; these assessments will be sent each morning and will be identical across treatment condition.

### **Participants' Use of Study Cellphones.**

Study cell phones will come activated with a 3-month pre-paid plan with Boost Mobile; these accounts will be maintained by Talaria. During this period participants will be assigned a phone number that will be linked to their URSI number in the Talaria database, but not to any identifying information. Cell phone plans will include unlimited minutes, texts and web access (this was the best option to avoid potential overage charges). Participants will also be allowed to keep their phone at the end of the study if they wish. However, to minimize the possibility of perceived coercion this will not be mentioned until after participants have enrolled in the study (i.e., after providing informed consent). Although participants will be allowed to use the phone for personal calls, texts, browsing, etc., they will be informed of certain limitations to cell phone use during the training provided at the baseline visit (see cell phone agreement form). For instance, participants will be instructed they cannot make international calls, cannot use the phone for illegal or unlawful purposes, and cannot attempt to sell, destroy or deface the phone during the course of the study. Over the course of the study, if the researchers deem that a participant is misusing the phone for these or other reasons, this may be grounds for removal from the study (as noted in the consent form). Once the participant completes the 8-week assessment they will be deemed discharged from the study and will no longer receive text messages from the study. They may continue to use the plan until it expires, at which point the phone number and plan will no longer be active. At that point participants can do as they wish with the phone (e.g., seek another service plan, give it away, etc.). If a participant discontinues the study before the 8-week appointment, they may be asked to return the phone at the discretion of the investigators. However, the investigators will not have any recourse for ensuring return of the phone. If the participant does not return the phone after a maximum of three phone call requests, we will not follow up further.

---

ii) Describe methods by which data will be managed - stored and destroyed.

